### Outcomes

#### Primary Outcome

Pain intensity is the primary outcome and will be captured using the 0 to 10 NRS score. The analysis metric will be the change in pain intensity from baseline (preintervention) to immediately after each intervention and 30 minutes later.

Hand massage routine protocol.1. Hygiene: Wash hands with warm water.2. Hold/connect/breathe: Make initial contact with patient, embrace hand, take a deep breath, and place feet on floor.3. Apply cream to entire hand, dorsal and palmer aspects, including phalanges.4. Spread (5 times) dorsal aspect of hand, using thumbs like opening a book. Repeat 5 times on palmer aspect, using the other 4 fingers to grip and glide. Spread again 5 times dorsal aspect of hand and 5 times palmer aspect.5. Gently shake bottom hand; vibration will help the patient relax and let go of any tension.6. Rotate wrists 3 times in each direction. Hold wrist with one hand while the other holds the patient’s hand and facilitates the passive rotation.7. Stretch the carpal ridge 3 times along wrist crease.8. Caterpillar walk on the dorsal aspect of the hand, between the bones (ie, zoning).9. Pinch (dorsal/palmer) aspect of the hand in between the metacarpals.10. Gently pull the webs of fingers.11. Knead (rock and roll) by making a fist on the palmer aspect of patient’s hand, gently rotate using the knuckles to apply pressure 5 times.12. Caterpillar walk on all areas of the palm, working proximally (towards the body) (if patient is less comfortable with palm upwards continue with hand in a neutral position, palm down).13. Make small circles along the 5 zones of the palmer surface of the hand (proximal to distal).14. Targeting key reflex areas, PRESS AND RELEASE 2 times in each area:  a. Shoulder-neck ridge (base of fingers)  b. Solar plexus (center of palm, just below the knuckle), PRESS and SPREAD (diaphragm line—moving outwards in both directions) 5 times  c. Lateral aspect of palm  d. Medial aspect of palm  e. Pad of thumb14. Pinch lateral aspect of hand 3 times.15. Caterpillar walk on the medial border of thumb 3 times.16. Caterpillar walk on the fingers:  a. Caterpillar walk proximal making sure to cover all surface areas.  b. Rotate knuckles gently 3 times in each direction (proximal to distal).  c. Gently pull fingers.17. Finishing touches: SWEEP entire hand, HOLD, and switch to other side.18. Hygiene: Once both hands have been massaged, wash hands with cold water.

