### Data Collection

Sociodemographic (eg, age, gender) and medical-surgical data (eg, type of cardiac surgery, analgesia) will be collected using standardized data collection sheets. Prior to the delivery of each intervention (hand massage or hand-holding) and before the first data collection for the standard care group, patients will complete a self-administered data collection sheet with 5 short questions using the NRS for the self-report of pain intensity, pain unpleasantness, and anxiety, a body map for identifying the site of pain, and an open-ended question for a description of the quality of pain. The interventionist will be masked to patients’ self-reports, which will be accessed only at the end of data collection to verify for missing data. The form will be completed before, immediately after the intervention (hand massage or hand-holding), and 30 minutes later, for a total of 3 data collection points per intervention. Those assigned to standard care will complete the form at similar times. This bundle of assessments will be repeated for each of the 3 interventions. Muscle tension and vital signs will also be evaluated at the same assessment points.

Finally, pain interference will be evaluated using a structured interview using the BPI on the second postoperative day to examine any carry-over effects.

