### Data Analysis

The data will be entered in the SPSS software version 22.0 (IBM Corp), and a random subset of data will be used to identify missing or erroneous values. This study aims to use intention-to-treat analysis by including every participant who has been randomized, regardless of group assignment, study withdrawal, or protocol deviations.

Descriptive statistics will be calculated for sociodemographic and medical-surgical data and the baseline scores on all the outcome variables. Group differentiation in sociodemographic and medical-surgical characteristics for participant patients will be investigated using chi-square tests of independence for nominal level variables and one-way analyses of variance (ANOVA) for interval and ratio level variables. If group differences exist, the respective variable will be included as a covariate in the subsequent analyses. Frequencies and percentages of the location and descriptors of pain (ie, sensory dimension of pain) will be calculated for each group and assessment point and used to describe the pain characteristics of participants. Data on pain location and quality will be compared over time.

Repeated measures between ANOVA factors will be used to test for treatment (hand massage, hand-holding, rest), time (before, immediately after, and 30 minutes later), and interaction effect for pain intensity, pain unpleasantness, muscle tension, anxiety, and means of vital signs. This will be run for each intervention and each of these outcome variables. One ANOVA test will be performed for pain interference with the independent variable being group assignment (hand massage, hand-holding, standard care). The main comparison of interest is between the hand massage and standard care group and the difference in means pre- and immediately posttreatment.

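### Covariates are chosen by significance tests of randomised baseline characteristics instead of being named in advance, and baseline pain is used by subtraction rather than as a covariate

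*Protocol article*

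**What the plan says.** The Data Analysis section of the protocol article screens patient characteristics between the arms: "Group differentiation in sociodemographic and medical-surgical characteristics for participant patients will be investigated using chi-square tests of independence for nominal level variables", with one-way ANOVA for interval and ratio variables. The rule that follows is "If group differences exist, the respective variable will be included as a covariate in the subsequent analyses". It gives no significance threshold, no list of candidate variables and no covariate that enters regardless of the result. The Data Collection section gives only examples of the candidates: "medical-surgical data (eg, type of cardiac surgery, analgesia) will be collected using standardized data collection sheets".

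Baseline outcome scores are outside this screen. They are summarised: "Descriptive statistics will be calculated for sociodemographic and medical-surgical data and the baseline scores on all the outcome variables". Baseline pain is nevertheless used, in two ways. Under Primary Outcome, "The analysis metric will be the change in pain intensity from baseline (preintervention) to immediately after each intervention and 30 minutes later". In the Data Analysis section, the pre-intervention score is a level of the time factor in the repeated measures ANOVA: "time (before, immediately after, and 30 minutes later), and interaction effect for pain intensity". That ANOVA is run separately for each intervention session. The main comparison is massage against standard care on the difference from before to immediately after treatment.

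**The concern.** Allocation is randomised and concealed, so any true baseline difference between arms is due to chance. A test of that difference answers a question whose answer is already known and says nothing about whether the variable predicts pain. The rule therefore admits irrelevant variables that happen to be imbalanced and leaves out prognostic ones that happen to be balanced. Which model is fitted is decided by the data.

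The screen also bypasses the variable most likely to predict later pain, the pain score before treatment. Subtracting that score fixes its slope at 1, whereas a covariate lets the slope be estimated. At stake are a primary model that is not known until the data are in, and precision that could be had from data already collected.

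There is one further exposure. Analgesia is listed among the medical-surgical data. If some of it is recorded after randomisation, the rule could admit a variable that treatment has affected.

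**Working it through.** **Inputs from the protocol article.** Sample Size and Sampling Procedure: difference 1.5 points, SD 2.0, two-sided 0.05, power 0.80, three equal arms, three measurements, minimum 72 patients (24 per arm), 79 after dropout. Not given, and therefore assumed: the number of characteristics tested, the threshold, and every correlation.

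**The plan's own figure.** For a between-groups test with repeated measures, λ = f²·N·m / (1 + (m − 1)ρ), with 2 and N − 3 degrees of freedom. Assume arm means 0, 0.75 and 1.5, so f = 0.75/√6 = 0.306, and ρ = 0.5. At N = 72 and m = 3, λ = 0.09375 × 72 × 3 / 2 = 10.1, and 72 is the smallest N that reaches 80% power. The stated figure can thus be reproduced, but only with a middle-arm mean and a ρ that the article does not state. The dropout step is 72 × 1.1 = 79.2.

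**Chance entry of a covariate.** For K independent tests at 5%, P(at least one significant) = 1 − 0.95^K.
- K = 5: 0.23
- K = 10: 0.40
- K = 20: 0.64

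**Effect of the rule on the test.** These are simulations with 24 per arm.
- Ten non-prognostic candidates, correlation 0.5 between pre and post scores: type I error stayed near 5%. Power was 72% for the change score and 70% for the change score plus the rule.
- One prognostic candidate, outcome analysed without subtraction: see the table. The ranges cover separate simulation runs.

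| Correlation of covariate with outcome | Type I error, rule | Type I error, covariate fixed | Power, rule | Power, covariate fixed |
|---|---|---|---|---|
| 0.5 | 4.5–4.9% | about 5% | 73% | 83–84% |
| 0.7 | 4.0–4.1% | about 5% | 74% | 94–95% |

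With no covariate at all, power in this setting is 72% by the noncentral t. The rule adds one or two points; fixing the covariate adds about 12 or 22.

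**Subtraction against covariate, same baseline score.** With correlation r between that score and the outcome:
- SD of the change score = 2.0·√(2(1 − r))
- residual SD with the score as covariate = 2.0·√(1 − r²)
- ratio of variances, covariate to change = (1 − r²) / (2(1 − r)) = (1 + r)/2, which is below 1 for every r below 1.

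Power for massage against standard care (noncentral t, 24 per arm, 1.5 points):

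| r (assumed) | SD, change | SD, covariate | Power, change | Power, covariate |
|---|---|---|---|---|
| 0.3 | 2.37 | 1.91 | 0.58 | 0.76 |
| 0.5 | 2.00 | 1.73 | 0.72 | 0.84 |
| 0.6 | 1.79 | 1.60 | 0.81 | 0.89 |
| 0.7 | 1.55 | 1.43 | 0.91 | 0.95 |
| 0.8 | 1.26 | 1.20 | 0.98 | 0.99 |

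Below r = 0.5 the change score has less power than ignoring baseline (0.72).

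**Which pre score.** The table holds when both methods use the same score. Table 1 places session 1 on the evening of surgery and session 3 late the next evening, and the sample size refers to the score immediately after the third massage. Suppose instead that the planned contrast is within session, with r of 0.6, 0.7 or 0.8, and that the covariate is the score before session 1, with r of 0.2, 0.3 or 0.4 to the score after session 3. The same formulas then give 0.81, 0.91 and 0.98 for the within-session change and 0.74, 0.76 and 0.79 for the covariate analysis. These are different questions as well as different powers.

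**The case against.** The strongest reply is that the power table does not test the recommended covariate at the time point the trial is powered for. If change is measured within each session, it spans little more than the 20 minutes of treatment and its correlation may be high; the score before session 1 is a day old by session 3 and may correlate weakly. On the illustrative correlations above, the planned contrast would have more power. This stands. The efficiency result is firm only for one and the same baseline score, and a gain at session 3 is not assured.

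A second reply is that change from baseline is unbiased under randomisation, so the choice concerns efficiency and is not an error. That also stands, and the gain is small at high correlation: about 4 points of power at 0.7 and 1 point at 0.8.

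Three stronger readings are tempting and are not supported:
- A reader might infer that the selection rule makes the primary P value too small. The simulations show type I error at or slightly below 5%.
- A reader might infer that baseline pain is ignored. It is subtracted, and it is a level of the time factor.
- A reader might take 40% as a property of this trial. It depends on an assumed ten independent tests at an assumed 5%.

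None of these replies defends the rule itself. It is stated text, so it cannot be put down to detail left for an analysis plan that is not shown.

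**Conclusion.** The point holds as a defect of pre-specification with a cost in precision; the validity of the test is not in question. The covariates depend on chance imbalance, with a 23% to 64% probability of at least one chance entry for 5 to 20 independent tests at 5%. The rule recovers one or two points of power where a prognostic covariate fixed in advance would give about 12 to 22, at assumed correlations of 0.5 and 0.7, and it leaves the test slightly conservative.

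Using baseline pain as a covariate is more efficient than subtracting the same score at any correlation below 1. The size of the gain rests on a correlation the article does not give. For sessions 2 and 3 the article does not settle which pre-intervention score counts as baseline, and the benefit of the session 1 score there is unknown. The change is worth making before the data are analysed, but should not be presented as a guaranteed rise in power.

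**What to change.** 1. Delete the chi-square and ANOVA tests of baseline characteristics and the covariate rule that depends on them. Describe baseline by arm without P values.
2. Name the covariates now: the pain score before session 1 for pain intensity, and the matching score for each secondary outcome measured at that point. Pain interference is first measured on the second postoperative day and has no such score. Where the score becomes a covariate, remove it from the levels of the time factor.
3. State which pre score defines baseline for sessions 2 and 3. The scores before those sessions follow earlier treatment. Adjusting for them answers a within-session question and may remove part of a cumulative effect, so such an analysis should be labelled accordingly.
4. Exclude from the covariates any variable recorded after randomisation, including later analgesia.

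The score before session 1 precedes all treatment, and the Recruitment of Participants section places baseline collection before random assignment, so no new data are needed. The cost is a change of analysis wording and about one degree of freedom. If the primary question moves from within-session change to pain after session 3 adjusted for the first score, that is a change of estimand and should be declared as one.

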### Background

Cardiac surgeries, such as coronary artery bypass grafting and valve replacement, rank among the most frequently performed surgical interventions worldwide [12] and necessitate the routine admission of patients to the ICU. Cardiac surgeries are commonly indicated to reduce anginal pain, but the surgical procedure itself can lead to the development of postoperative pain. Mounting evidence shows that cardiac surgery ICU patients experience moderate-to-severe pain reaching proportions as high as 74% despite the use of analgesics [2-5], with the highest pain intensity commonly experienced in the first 24 hours postsurgery [13].

Unrelieved postoperative pain can interfere with patients’ ability to cough and mobilize effectively, which predisposes them to postoperative complications such as atelectasis, pneumonia, and deep vein thrombosis [2,5,14], thereby delaying recovery and ICU discharge. Moreover, the intensity of acute postoperative pain immediately after surgery is a significant predictor of the presence and severity of persistent postoperative pain up to 2 years postsurgery [15-17], a serious and often unrecognized complication after cardiac surgery that may interfere with daily activities and quality of life [18].

Among the pharmacological approaches to pain control, opioids constitute the mainstay of treatment in the ICU [19,20], yet pain has been shown to persist even during unrestricted use of these analgesic agents [13,21]. The use of complementary nonpharmacologic interventions such as massage has been suggested in the clinical practice guidelines of the Society of Critical Care Medicine given their opioid-sparing and analgesia-enhancing potential [20]. Massage has been defined as the manual manipulation of muscles and soft tissues of the body through the application of various systematic and rhythmic hand movements [22,23].

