#### Passive Control Group

The passive control group will receive the standard care administered in the ICU including a 20-minute rest period including the environmental adjustments of the experimental and active control groups. The interventionist will be outside of the patient room and have no contact with the patient throughout the 20 minutes. The standard care includes the pharmacological and nonpharmacological treatments (eg, repositioning) used to promote recovery and pain relief. In the study ICU, cardiac surgery patients are automatically prescribed a pain management protocol that includes the regular administration of morphine and breakthrough doses of analgesia as needed.

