### Concomitant Care

Concomitant interventions may be received by patients while participating in this trial. Consenting patients will be permitted to receive any of the pharmacological treatments prescribed by their treating physician and any of the nonpharmacological interventions offered in the ICU (eg, back rub), and such data will be recorded. It is not prohibited that patients participate concomitantly in other research studies unless it involves any form of complementary therapy.

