### Limitations

One of the anticipated limitations of this RCT is the lack of blinding of patients in the standard care group and the respective clinical personnel responsible for their care. Although environmental adjustments will be made, these patients will have already been informed of the 3 trial arms and their implications and could easily recognize their group assignment. Equally, it is expected that the ICU personnel will notice the absence of an active intervention and assume patient assignment to standard care. Given the unlikelihood of blinding related to the standard care group, patients could modify their self-report while the personnel could practice differently compared to when they see hand massage/hand-holding administrations, thereby increasing the risk of performance bias.

Only the cardiac surgery ICU patient population will be included in this RCT, which will limit the generalizability of the findings to other ICU patients. Even so, this study will reveal the effectiveness of massage in this group of ICU patients suffering from intense pain and should be a trigger for further research internationally on the use of this intervention in the ICU in addition to the locally established standard care.

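### The covariate rule is not limited to pre-randomisation values and its variable class includes analgesia, so the pain analysis could be adjusted for a consequence of treatment; analgesic use is also not an outcome

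*Protocol article*

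**What the plan says.** Under Data Collection, the protocol article states that "medical-surgical data (eg, type of cardiac surgery, analgesia) will be collected using standardized data collection sheets". Analgesia is one of two examples, and no time window is given.

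Under Data Analysis, "Group differentiation in sociodemographic and medical-surgical characteristics for participant patients will be investigated using chi-square tests of independence for nominal level variables", with one-way ANOVA for interval and ratio variables. The consequence follows directly: "If group differences exist, the respective variable will be included as a covariate in the subsequent analyses". The descriptive statistics are to cover "sociodemographic and medical-surgical data and the baseline scores on all the outcome variables"; in that phrase the word baseline attaches to the outcome scores only.

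Standard care in the study ICU includes "regular administration of morphine and breakthrough doses of analgesia as needed" (Passive Control Group). Under Concomitant Care, patients may receive any prescribed drug and "any of the nonpharmacological interventions offered in the ICU (eg, back rub), and such data will be recorded". Randomisation takes place on the evening of the day of surgery, and two of the three sessions follow on the next day (Table 1).

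The Background cites a guideline that suggests nonpharmacologic interventions such as massage "given their opioid-sparing and analgesia-enhancing potential". Analgesic use does not appear among the outcomes in the Objective, Primary Outcome or Secondary Outcomes sections, and Data Analysis does not analyse it as one.

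**The concern.** A covariate in a randomised comparison should be something treatment cannot change. Analgesia given after allocation fails that test twice: treatment may alter it, and it is itself a response to pain, the primary outcome. Adjusting for it blocks any part of the treatment effect that runs through dose. It also mixes in the reason why patients with more pain receive more drug.

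The trigger makes this worse. The rule brings a variable in when the arms differ on it, so a real effect of massage on analgesic use is what would make the adjustment likely. The protocol gives two reasons to expect a possible difference: the opioid-sparing rationale, and the Limitations section's remark that for the rest arm "the personnel could practice differently compared to when they see hand massage/hand-holding administrations".

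The outcome list has a related gap. With as-needed analgesia available in every arm, similar pain scores at different doses would be a finding in its own right, but no planned outcome is designed to show it.

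This is separate from the general objection to choosing baseline covariates by significance test. Here the variable may not be a baseline variable at all.

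**Working it through.** **1. What the text fixes.** Read together, the sections give this chain:
- analgesia belongs to the medical-surgical data (Data Collection);
- medical-surgical characteristics are tested between arms (Data Analysis);
- any that differ become covariates (Data Analysis).

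No section adds a limit to pre-randomisation values, and analgesia received after randomisation is among the treatments recorded (Concomitant Care). The rule therefore does not exclude it.

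**2. How often the rule would bring dose in.** The article's minimum of 72 patients gives 72/3 = 24 per arm. The 72 itself reproduces (power 0.802) with d = 1.5/2.0 = 0.75, the third arm midway (f = 0.306), three measurements and an assumed correlation of 0.5. It is not in dispute.

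For a one-way ANOVA screen at .05 (level assumed), the noncentrality for a massage-rest dose difference of s SD is 24s²/2 with hand-holding midway, and 24s²·2/3 with hand-holding equal to rest. The dose differences are assumptions:

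| Dose difference | Hand-holding midway | Hand-holding equal to rest |
|---|---|---|
| 0.5 SD | 0.31 | 0.40 |
| 0.7 SD | 0.56 | 0.69 |

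With no effect on dose, the simulated screen (24 per arm) triggered in 4% of trials and the mean estimate did not move.

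**3. What adjustment does to the estimate.** For a linear model, adjusted effect = total effect − (within-arm slope of pain on dose) × (arm difference in dose).

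Assume one SD of dose lowers pain by 0.5, underlying severity raises pain by 1.6 per SD, the severity-dose correlation is b, massage lowers dose by 0.7 SD, and the direct effect is -1.85. The total effect is -1.85 + (-0.5)(-0.7) = -1.5. The within-arm slope is -0.5 + 1.6b, so:

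adjusted = -1.5 − (-0.5 + 1.6b)(-0.7) = -1.85 + 1.12b

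| b | Adjusted | Against total -1.5 |
|---|---|---|
| 0 | -1.85 | larger by 0.35 |
| 0.3 | -1.51 | nearly equal |
| 0.5 | -1.29 | smaller by 0.21 |
| 0.7 | -1.07 | smaller by 0.43 |

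The sign changes at b = 0.35/1.12 = 0.31.

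**4. A second set of assumptions.** A simulation with a direct effect of -1.5, dose lowered by 0.8 SD, dose effect -0.5 and severity effect 1.5 has a total effect of about -1.1. The adjusted estimate was -1.51 at correlation 0, -1.13 at 0.3 and -0.88 at 0.5. With dose raised by 0.8 SD and correlation 0, the total was -1.91 and the adjusted estimate -1.51.

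**5. The change score.** The article's metric is change from the pre-session score. If that score carries the same 1.6 severity term and dose acts only on the later score, severity cancels. The slope in step 3 is then -0.5 at every b, and the adjusted estimate is -1.5 − (-0.5)(-0.7) = -1.85. Under that assumption adjustment enlarges the effect.

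The estimate moves off the randomised effect in most of these settings, but neither its direction nor its size is fixed.

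**The case against.** The strongest defence is that analgesia here means a pre-randomisation characteristic. It stands beside type of surgery as an example; the screened variables are called characteristics and are described together with baseline scores. Baseline data are collected before randomisation. Table 1 places the demographics questionnaire preoperatively and on the evening of surgery only, and drugs received during the trial come under a separate heading. This reading is possible. A reader might infer that the protocol lists post-randomisation analgesia as a covariate candidate, but the text does not say so. What stands is that the rule does not exclude it. Since the article states the rule itself, and in mandatory terms, this is not merely a detail left to a fuller document.

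A reader might also infer that adjustment would remove a real benefit. The document does not support a direction: with the assumptions above, the effect can be enlarged or reduced. It gives neither a dose difference nor a severity-dose correlation.

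Nor does it follow that an opioid difference would go unseen. If analgesia is in the screened class, it is already described and tested across arms. That part of the defence holds. But a comparability check whose consequence is adjustment is not the same as an outcome read beside pain.

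Finally, the cited support is modest. Opioid sparing is described as a potential of a class of interventions, and the remark about personnel does not mention analgesia. Both make an arm difference plausible; neither shows one.

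**Conclusion.** The point holds as a gap in a stated rule. The covariate rule is open to post-randomisation analgesia and, followed literally, could replace the randomised comparison of pain with one conditioned on a consequence of treatment. This needs three things: the analgesia screened includes doses given after allocation, the arms differ on it, and the analyst applies the rule as written.

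The size is not determinable from the document. The range of -1.85 to -1.07 against a true -1.5 shows that bias in either direction is possible under assumed inputs; it is not a forecast. The absence of analgesic use from the outcomes needs no inference and follows from the outcome sections themselves.

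This is a cheap improvement. It changes neither the sample size nor the care given.

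**What to change.** In Data Analysis:
- Restrict covariates to variables fixed before randomisation.
- State that analgesia given after randomisation is never a covariate in the outcome analyses.

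In Secondary Outcomes and Data Analysis:
- Add analgesic (opioid) use from randomisation through the third session, by arm, and read it beside the pain results. The article does not say whether dose amounts and times are recorded, so the measure should be defined to the extent the recorded data allow.

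The cost is a few lines of wording and one more secondary comparison.

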## Methods

### Trial Design

This research study is designed as a randomized, controlled, patient-blinded, single-center superiority trial with 3 parallel groups and a 1:1:1 allocation ratio. A modified Consolidated Standards of Reporting Trials flow diagram for individual RCTs of nonpharmacologic treatments will be used to document recruitment and retention of participants (see Multimedia Appendix 1) [43].

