### Sample Size and Sampling Procedure

A power analysis was conducted using the G*Power 3 program [38] to estimate the sample size required to capture the potential effects of massage to decrease the primary outcome (pain intensity) and to strengthen the statistical conclusion validity. The mean treatment difference was observed to be greater than 1.5 in several RCTs [11,26,39,40] and approximates the clinically significant difference of 2 points on the 0 to 10 Numeric Rating Scale (NRS) [41]. This trial is powered to be able to detect a difference in the pain intensity score of 1.5 between the hand massage and standard care group. The standard deviation of pain intensity scores is approximately a 2.0 value, which was selected for the sample size calculation. To detect a mean difference in pain intensity scores of 1.5 points (SD 2.0) immediately after the third massage with a 2-sided significance level of .05 and power of .80 with equal allocation to 3 arms and a repeated measures between factors context with 3 measurements would require a minimum of 72 patients.

Given the low attrition rates observed with this patient population (0% [9,10,30] and 35/287 (12.2%) [29]), a 10% drop-out rate is considered in the calculation of the total sample size. Therefore, the final size required for this RCT is 79, and it will be reached using convenience sampling.

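### The 80% power behind the 72 patients belongs to a treatment main effect that averages in the pre-intervention reading, not to the pre-to-post comparison named as the main one

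*Protocol article*

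**What the plan says.** All places are in the Methods of the protocol article.

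- **Sample Size and Sampling Procedure** gives the target: "This trial is powered to be able to detect a difference in the pain intensity score of 1.5 between the hand massage and standard care". On variability: "The standard deviation of pain intensity scores is approximately a 2.0 value". The effect is placed in time: "To detect a mean difference in pain intensity scores of 1.5 points (SD 2.0) immediately after the third massage". The error rates are "2-sided significance level of .05 and power of .80 with equal allocation to 3 arms". The test family and the resulting size are described as follows: "a repeated measures between factors context with 3 measurements would require a minimum of 72 patients". No correlation between readings and no hand-holding mean are given.
- **Data Analysis** specifies a repeated-measures ANOVA that "will be used to test for treatment (hand massage, hand-holding, rest), time (before, immediately after, and 30 minutes later"), and also the interaction. It is run separately for each of the three interventions. The section then states that interest centres on massage against standard care and on "the difference in means pre- and immediately posttreatment".
- **Outcomes, Primary Outcome** makes change from the pre-intervention reading the analysis metric.
- **Trial Design** has "3 parallel groups and a 1:1:1 allocation ratio", so 72 patients means 24 per arm.

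**The concern.** In a repeated-measures ANOVA the between-factors test compares arm means averaged over every level of time. Here one level is the reading taken before the intervention. Where the arms do not yet differ at that reading, it contributes a zero and dilutes the average. A calculation that assumes 1.5 points on average over three readings therefore overstates the power of this test for a 1.5-point effect that exists only after treatment.

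The quantity that the protocol singles out, the pre-to-post difference between two arms, is a different test with a different variance. Its power depends on a correlation that the article does not state. The 80% is thus attached to one test while the main question is put to another. The treatment effect, the interaction and the contrast can also disagree, and the article does not say which of them decides.

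**Working it through.** **Inputs from the protocol.** Difference 1.5; SD 2.0; two-sided alpha 0.05; 3 arms; m = 3 readings; N = 72, 24 per arm.

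**Assumptions, not in the protocol.** A common correlation ρ between readings, and the position of the hand-holding mean. Both are varied below.

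**Step 1: reproduce 72.** Take hand-holding midway, so the arm means are 0, 0.75 and 1.5. Their root-mean-square deviation is √[(0.75² + 0 + 0.75²)/3] = 0.612, so f = 0.612/2.0 = 0.306. For the between-factors test,

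λ = f² × N × m / [1 + (m − 1)ρ], with 2 and N − 3 degrees of freedom.

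At ρ = 0.5, λ = 0.09375 × 72 × 3/2 = 10.125 and power is 0.802. This reproduces 72. The inputs are not unique: hand-holding equal to another arm (f = 0.354) with ρ = 0.8 also gives 72 (power 0.813). A plain two-sample comparison does not reproduce it: it needs 28 per arm, 84 in all.

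**Step 2: same test, no difference at the reading before the session.** The averaged difference is (0 + 1.5 + 1.5)/3 = 1.0 if the effect persists to 30 minutes, and (0 + 1.5 + 0)/3 = 0.5 if it does not. So f is multiplied by 2/3 or 1/3. At ρ = 0.5, λ becomes 10.125 × 4/9 = 4.5 or 10.125 × 1/9 = 1.125.

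| Power of the treatment main effect, N = 72 | ρ = 0.3 | ρ = 0.5 | ρ = 0.7 |
|---|---|---|---|
| Hand-holding midway, effect immediately after only | 0.16 | 0.14 | 0.12 |
| Hand-holding midway, half remains at 30 min | 0.32 | 0.27 | 0.23 |
| Hand-holding midway, all remains at 30 min | 0.54 | 0.44 | 0.38 |
| Hand-holding equal to another arm, all remains | 0.67 | 0.56 | 0.49 |

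No case checked reaches 0.80.

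**Step 3: the interaction test** (4 and 138 degrees of freedom, hand-holding midway). Power is 0.51 to 0.65 at ρ = 0.5, depending on how much effect remains at 30 minutes, and 0.76 to 0.98 at ρ = 0.7 to 0.8. With hand-holding equal to another arm it is 0.65 to 0.79 at ρ = 0.5.

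**Step 4: the named comparison and the alternative** (two arms, 24 each). The noncentrality is 1.5/[SD × √(2/24)]. The SD is 2√[2(1 − ρ)] for the unadjusted change and 2√(1 − ρ²) for the post score adjusted for a pre score. Example for the change at ρ = 0.5: SD = 2.0, noncentrality = 1.5/(2.0 × 0.2887) = 2.598, power 0.72.

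| ρ | Unadjusted change | Adjusted post score |
|---|---|---|
| 0 | 0.44 | 0.72 |
| 0.3 | 0.58 | 0.76 |
| 0.5 | 0.72 | 0.84 |
| 0.6 | 0.81 | 0.89 |
| 0.7 | 0.91 | 0.945 |

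In each column ρ is the correlation between the post score and the pre score used in that analysis.

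**Step 5: carry-over.** The sized effect follows the third massage, so that session's pre reading comes after two earlier sessions. If, as an illustration, the arms already differ by 0.5 there, the change contrast is 1.5 − 0.5 = 1.0. Its power falls to 0.40 at ρ = 0.5 and 0.59 at ρ = 0.7. The main effect would then be diluted less than in step 2.

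**The case against.** The strongest reply is that nothing in the protocol makes the treatment main effect the efficacy test. The same sentence also tests the interaction. The Primary Outcome section works with change from pre-intervention, and the main comparison is named as a pre-to-post difference between two arms. Neither the interaction nor that contrast is diluted by equal arms beforehand. That stands. A reader might infer from step 2 that the trial has 14% to 44% power for its question; the documents do not support that, because the figure belongs to one of several planned tests.

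Two further points also stand:

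- **Equality before treatment.** It is secured by randomisation only in the first session. For the third session, where the effect is sized, carry-over may make the main effect less diluted. The same carry-over shrinks the change contrast, so it does not restore the stated power.
- **Inferred inputs.** The correlation and the hand-holding mean are not given, and the 3 measurements could mean the three sessions rather than the three readings within one. At the alternative ρ of 0.8 that also yields 72, the change contrast has power 0.98.

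What the reply does not remove is the mismatch. On every route found to 72, the 80% refers to a between-factors average and not to the comparison that the protocol names.

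**Conclusion.** The point holds as a mismatch between the power statement and the main comparison. The figure of 72 reproduces for a treatment main effect with 1.5 points averaged over all three readings. With no difference at the reading before the session, that test has about 14% to 44% power at ρ = 0.5 with hand-holding midway, and at most about 67% over the other assumptions checked.

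The named change contrast is much better placed but is not shown to have 80%. It is about 8 points short at the ρ of 0.5 that reproduces 72 with hand-holding midway, reaches 80% at about 0.6, and exceeds it above that. These figures assume no carry-over into the third session's pre reading, 24 analysed per arm, and a common SD of 2.0. The protocol supports neither a claim that the trial is badly underpowered nor a claim that its main comparison has the stated 80%.

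**What to change.** 1. State that the treatment main effect of the ANOVA is not the efficacy test.
2. Make the confirmatory test the massage-minus-standard-care contrast in pain intensity immediately after the third session. Use the POD 0 score taken before the first session as a covariate and not as a level of time. No study intervention can have affected that score, so carry-over does not distort the contrast.
3. Keep the 30-minute reading as secondary in the same model, and align the Primary Outcome wording with the POD 0 reference.
4. Restate the power for this contrast together with its assumed correlation: about 0.72 at 0, 0.76 at 0.3, 0.84 at 0.5 and 0.945 at 0.7.

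The cost is analysis wording; no new data are needed. Two limits should be stated openly. The correlation between the POD 0 score and the score after the third session, in the late evening of POD 1, is undocumented and may be low. Below about 0.42 the stated power falls somewhat under 80%. Adjustment also beats the unadjusted change at every correlation in step 4 when both use the same pre score. If the third session's own pre score correlates much more strongly with the outcome and there is no carry-over, the change could do better.
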